#### Sample size estimates

Sample size estimates (alpha 0.05, beta 0.20) are based on planned comparisons for the main effects of PRT and CT, as well as the effect of combined training vs. either intervention in isolation on our primary outcome: global cognitive function as assessed by ADAS-Cog. The assumptions are as follows: our meta-analyses [30] and review of published RCTs in older adults [15] reveal Effect Sizes (ES) for a range of cognitive outcomes of approximately 0.60 for cognitive training, 0.59 for aerobic/resistance training, and 0.53 for resistance training, compared to 0.15 for control groups. However, as we are enrolling a cohort with early cognitive impairment, we anticipate a decline of approximately this magnitude (ES = 0.15) over 12 months in our sample, so that the sham control condition would merely offset that decline (ES = 0.0). Thus, we have conservatively powered the study to show an ES of 0.53 for the main effects of both CT and PRT vs. control (n rounded up to 30/group × 4 = 120 required for 4-cell factorial design).

The only two published studies of *combined mental and physical training *[12,16] showed average ES = 0.94 for combined training compared to mental training alone and ES = 1.27 for combined training compared to exercise training alone. Therefore, we have ample power (99.7%) to find a difference of this magnitude between our combined training (n = 30) and isolated training groups (n = 30). Reported dropout from drug trials in MCI is 28% [31] however our experience in fully supervised training of older adults with frailty/chronic disease dropout averages 10-15% over 12 months. Therefore, we will inflate sample size needs for approximately10% drop out rate to account for anticipated attrition (n = 132), and we will recalculate these sample size needs in interim analysis after the first 50 participants have completed 6 months intervention and revise ES and sample size needs if required.

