### Statistical Analysis

We will use an intention to treat (ITT) analytic strategy as our primary analytic treatment of the data. However, we acknowledge the potential bias of any method of imputation [last observation carried forward (LOCF), mean of group, expectation maximization algorithm (EM)] or restriction to observed cases (complete case analysis). Therefore, we will make all attempts to retrieve data from dropouts by obtaining final measures regardless of intervention participation or compliance, and will use the EM method for data missing at random. In addition, we will compare characteristics of dropouts to completers and perform secondary sensitivity analyses (completers, and per-protocol analyses) to examine potential for dropouts and imputation to bias the results.

Mixed modelling of 6- and 18-month outcomes, adjusted for baseline values and any potential confounders identified will be constructed to test our primary and secondary hypotheses. We will test for main effects of CT and PRT, as well as for the interaction term (CT × PRT) to identify isolated and combined training arm significance and effects sizes. Relationships of interest and risk factors for changes in cognitive function and other secondary outcomes will be analysed with simple and multivariate linear and logistic regression models as appropriate. Weighted mean differences, 95% Confidence Intervals and Effect Sizes will be calculated for all outcomes, and clinical meaningfulness will be assessed in light of available data on the expected annual rates of change in this cohort for all known primary and secondary outcome variables.

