## Results

We originally estimated the need for a sample size 10% larger than our expected effect size required (n = 132). With our retention rate of >90% to date our recruitment target remains appropriate 120/.90 = 133. Thus, we have recruited 80/133, 60% of our planned cohort to date. Compliance with training sessions to date has been high for all groups with median compliance ranging from 78.44% for sham physical/CT to 100% for PRT/CT. Furthermore there has been one adverse event reported thus far (one rotator cuff injury managed conservatively) in PRT group, and no adverse events during assessments, CT, or sham interventions.

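### The planned checks for dropout bias never relax the missing-at-random assumption, so their agreement with the primary analysis can look reassuring without grounds

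*Protocol article*

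**What the plan says.** The Statistical Analysis section of the protocol article makes intention to treat the primary strategy. It concedes that any imputation, and any restriction to observed cases, can be biased. It then commits to four things:

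- **Retrieval:** "we will make all attempts to retrieve data from dropouts by obtaining final measures regardless of intervention participation or compliance".
- **Imputation:** it "will use the EM method for data missing at random".
- **Model:** "Mixed modelling of 6- and 18-month outcomes, adjusted for baseline values and any potential confounders identified", testing the two main effects and the CT × PRT interaction.
- **Checks on bias:** it plans to "perform secondary sensitivity analyses (completers, and per-protocol analyses) to examine potential for dropouts and imputation to bias the results". Alongside these, those who leave are to be set against those who stay on their recorded characteristics.

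The Sample size estimates section allows about 10% dropout. It reports 10–15% over 12 months in the team's own supervised training studies and 28% in drug trials in MCI. The Results section gives interim retention above 90% and "median compliance ranging from 78.44% for sham physical/CT to 100% for PRT/CT".

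**The concern.** The last commitment names both a purpose and the tools for it, and the tools do not fit the purpose.

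EM and the likelihood-based mixed model assume that, given what was observed, those who left would have scored like similar people who stayed. A completer analysis drops the leavers and needs missingness assumptions at least as strong. A per-protocol analysis also selects on attendance, which on the interim figures differs between arms, so a gap between it and the ITT result cannot be read as dropout bias. Comparing dropouts with completers uses only characteristics that were seen. No step asks what happens if the unseen scores were worse than predicted.

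This matters because the cohort is chosen for risk of decline, so withdrawal linked to decline after the last attended visit is plausible. Follow-up runs to 18 months, longer than the 12 months behind the 10–15% figure. If such withdrawal were more selective in the active arms than under double sham, the primary and completer estimates would err together in favour of training. Their agreement could then be reported as robustness.

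**Working it through.** **1. The plan's own sample size.** Two-sided alpha 0.05, power 0.80, effect 0.53 SD: n per factor level = 2 × (1.96 + 0.84)² / 0.53² ≈ 56. That is 112 in total and 28 per cell, which the article rounds up to 30 (120 in total). Then 120 × 1.10 = 132. The figures reproduce, and each main effect compares 60 with 60.

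**2. Simulation set-up.** The article gives no correlations and no dropout mechanism, so these are assumptions: SD 1, correlations 0.65–0.70 between visits, zero true effect, and 4,000 trials per scenario. Where loss is selective, the chance of missing the 18-month visit is weighted by exp(1.5 × 18-month score), with higher scores worse. Elsewhere loss is random. The primary analysis is imitated by missing-at-random imputation from baseline, 6-month score and arm, and the completer analysis by regression adjusted for baseline.

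**3. Selective loss at one factor level only, random at the other.** Bias in favour of training, in SD:

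| Loss | Primary | Completers | Difference |
|---|---|---|---|
| 10% | 0.059 | 0.074 | 0.015 |
| 15% | 0.090 | 0.113 | 0.023 |
| 28% | 0.170 | 0.209 | 0.039 |

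Dividing the primary bias by the loss share (0.059/0.10, 0.090/0.15, 0.170/0.28) gives about 0.6 SD each time. That is how much worse the missing scores are than predicted; call it δ.

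**4. The actual 2×2 design.** The comparator for CT is half PRT-only and half double sham. If all three active cells lose decliners, both CT cells carry the bias and so does one of the two comparator cells:

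bias ≈ loss × δ × (1 − ½)

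With δ = 0.6 this is 0.03, 0.045 and 0.084 SD. Simulating four cells of 30 gives about 0.03, 0.05 and 0.08 SD. Halving the completer column gives about 0.04, 0.06 and 0.10 SD, so primary and completer estimates differ by about 0.01 to 0.02 SD here and by up to 0.04 SD in step 3.

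**5. Two variations.** If half the dropouts' outcomes are retrieved, the bias in step 4 falls to about 0.02 to 0.04 SD. If the same dropout rule applies in every arm, it is about zero under no true effect.

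**6. Does agreement or disagreement tell us anything?** A second simulation used other assumptions: correlations 0.7/0.6/0.7 and loss driven by unseen decline from baseline. It compared two levels of one factor with a true effect of 0.53.

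- Loss depending only on observed scores: the primary analysis is right (0.53 at 10% loss, 0.52 at 28%), but completers give 0.50 and 0.46.
- Loss depending on unseen decline by the same rule in both levels: primary 0.47 and completers 0.46 at 10%, 0.42 and 0.40 at 28%. They agree, and both are too small.
- Loss depending on unseen decline in the active level only: 0.61 and 0.635 at 10%, 0.75 and 0.80 at 28%. They are close, and both are too large.

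So the check can disagree when the primary analysis is sound and agree when it is not. In the same runs dropouts differed from completers at baseline by 0.3–0.7 SD when loss depended on unseen decline and by about 0.5 SD when it depended on observed scores. That comparison cannot separate the two either.

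**7. What a tipping-point analysis would report.** The critical difference at 60 v 60 is 1.96 × √(2/60) = 0.36 SD (held fixed). An observed 0.53 leaves a margin of 0.17 SD. If only the level receiving the factor is shifted, significance is lost at 0.17/0.10 = 1.7 SD, 0.17/0.15 ≈ 1.15 SD or 0.17/0.28 ≈ 0.6 SD. Readers can judge whether shifts of that size are plausible.

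**The case against.** **Retrieval.** The article's main defence is to collect outcomes from people who leave. This stands: step 5 shows it roughly halves the bias if half are retrieved. It does not test whatever stays missing.

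**The factorial design.** Much of the bias cancels because PRT-only participants sit in the CT comparator, and the reverse. This stands, and step 4 carries it.

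**Exposure.** B-IADL comes from an informant, and a telephone version is used at screening, so it need not be lost when a participant stops attending. Training ends at 6 months and the article promises all groups equal contact over 18 months, so arm-differential loss in the later year is an assumption. The 28% comes from drug trials and is set against the team's own lower experience. All of this limits the likely size. None of it makes the named analyses able to detect the problem.

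**Purpose.** The stated aim also covers bias from imputation, and setting EM beside a non-imputed analysis does show how far imputation moves the estimate. That is a reason to keep the completer analysis, though not to treat it as a test of the missingness assumption.

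**Placement.** Details of a tipping-point analysis often sit in an analysis plan, which is not shown. That is fair, and the absence of such detail is not the point. The point is that the article assigns the dropout-bias question to methods that cannot answer it.

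**Conclusion.** The point holds as a limited one. Completer and per-protocol analyses, and the comparison of characteristics, cannot show whether the missing-at-random result survives decline-related withdrawal.

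Under selective loss in the three active cells, the bias in a main effect is small at the planned 10% loss (0.03/0.53, about 6% of the planning effect) and moderate at 28% (0.08/0.53, about one sixth). These sizes rest on assumed correlations and an assumed dropout rule.

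A reader might infer that the checks will certainly reassure, or that the trial faces bias of a third of its planning effect (0.17/0.53). The documents support neither. The larger figure needs 28% loss, selective at one factor level and purely random at the other, with nothing retrieved. The article reports no such pattern, and its interim retention is above 90%. Per-protocol results may also differ from ITT for reasons of attendance. What can be said is that the checks can look reassuring when they should not.

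**What to change.** - Keep the retrieval of outcomes from dropouts.
- Keep the completer and per-protocol analyses as supplementary, and do not present them as evidence of robustness to dropout.
- Add a prespecified delta-adjusted (tipping-point) multiple imputation for ADAS-Cog and B-IADL at 6 and 18 months. Set shifts separately for each of the four cells, so that it is clear how PRT dropouts count in the CT contrast and the reverse. Include a scenario that shifts only the cells receiving the factor under test.
- Add a version that imputes active-arm dropouts from the double-sham cell.
- Report the shift at which each primary conclusion changes.

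The cost is some plan wording and a few extra model runs, with no new data. The downside is that a positive result may have to be reported as less robust.

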## Results

We originally estimated the need for a sample size 10% larger than our expected effect size required (n = 132). With our retention rate of >90% to date our recruitment target remains appropriate 120/.90 = 133. Thus, we have recruited 80/133, 60% of our planned cohort to date. Compliance with training sessions to date has been high for all groups with median compliance ranging from 78.44% for sham physical/CT to 100% for PRT/CT. Furthermore there has been one adverse event reported thus far (one rotator cuff injury managed conservatively) in PRT group, and no adverse events during assessments, CT, or sham interventions.

## Discussion and conclusions

Recruitment of subjects has been challenging, with less than 4% of contacts recruited, and 12 telephone screening interviews required for each subject enrolled. However, the most common reasons for ineligibility have been lack of cognitive impairment, or being too physically active, rather than medical exclusions, attesting to the potential generalizability of this volunteer sample to typical older adults with multiple stable chronic illnesses and mild cognitive impairment.

Our primary outcomes of global cognitive status and functional independence are anticipated in 2012. This information will provide novel and robust evidence for the efficacy of cognitive and strength training on cognition and functional status in at risk older adults. This study conforms to all CONSORT criteria for the reporting of RCTs, making it relatively unique in the field to date. Furthermore, the SMART trial will provide valuable information on the persistence of training benefits after cessation of training at 18 months. Recording participant social and recreational activities will also enable SMART to examine the impact of training post intervention on leisure activity, and control against potential confounding effects of participants independently pursuing physical exercise and mental activities.

Our secondary outcomes will enable the first comprehensive investigation of the relative and combined benefits of physical and cognitive training on brain morphology and function, anxiety and depressive symptoms, self-efficacy, quality of life, body composition, cardiovascular risk profile, aerobic and musculoskeletal fitness, and metabolic health. These outcomes will not only provide evidence of the potentially broad benefits of the SMART interventions in this cohort, but also clarify the hypothesized mechanisms contributing to any observed cognitive outcomes.

In summary, SMART will test a non-pharmacological preventative intervention that targets older adults at high risk of cognitive decline. By implementing a regime of physical and mental exercise, we aim to empower the individual, contribute to their physical, cognitive and psychological health, and ultimately improve quality of life.
